### Objectives {7}

#### Primary objective

To demonstrate non-inferiority in the efficacy of Dilapan-S® (12 h or 24 h insertion) to Propess for outpatient induction of labour at 39 weeks’ gestation in otherwise uncomplicated, normal risk* nulliparous women.

*A pregnancy is considered “normal-risk” when there are no active complications and there are no maternal or fetal factors that place the pregnancy at increased risk for complications. Specifically, the following conditions should be met to consider a pregnancy to be normal risk:Singleton pregnancyCephalic presentationTerm gestation (37–39 weeks gestational age)Maternal pre-pregnancy body mass index < 35 kg/m^2^Maternal age of ≥ 18 and < 40 yearsNo evidence of the following conditions:◦ Pre-pregnancy diabetes◦ Gestational diabetes◦ Pre-pregnancy hypertension◦ Preeclampsia◦ IUGR◦ Oligohydramnios◦ Cervical cerclage in situ◦ Premature rupture of membranes◦ Congenital fetal anomaliesAbsence of other active obstetric complication not mentioned above

#### Secondary objective(s)

To compare the Dilapan-S® (12 h) group to the Propess group in the primary endpoint and secondary endpoints.To compare the Dilapan-S® (24 h) group to the Propess group in the primary endpoint and secondary endpoints.To compare the Dilapan-S® (12 h) group to the Dilapan-S® (24 h) group in the primary endpoint and secondary endpoints.To compare rates of vaginal delivery in the Dilapan-S® 12-h group, the Dilapan-S® 24-h group, and the Propess group at 36 h, 48 h, and 48 h respectively from insertion time to delivery. 

### Trial design {8}

This study is an open-label parallel group single-centre non-inferiority trial.

Participants are normal risk nulliparous women who have no pregnancy-related or medical contraindication to IOL. Women will be randomised to one of three induction groups—Dilapan-S® (12-h insertion or 24-h insertion) or Propess, which will be initiated between 39+0 and 39+4 weeks’ gestation, and then allowed to return home for either 12 or 24 h. They will be readmitted 12/24 h later and reassessed in order to continue with induction of labour.

Patient recruitment will take place over 30 months within a single centre. The study will recruit a maximum 109 women for each study arm. Total duration of participants’ involvement in the trial will be 8 weeks to allow for postpartum follow-up.

## Methods: participants, interventions, and outcomes

### Study setting {9}

This trial will be conducted at the Rotunda Hospital, a large tertiary referral centre in Dublin, Ireland.

### Eligibility criteria {10}

#### Inclusion criteria

In order to be eligible to participate in this study, an individual must meet all of the following criteria:Provide signed and dated informed consent formWilling to comply with all study procedures and be available for the duration of the studyNormal risk nulliparous women (as defined in trial objectives)Age ≥ 18 and < 40 yearsSingleton pregnancyNo contraindications to induction of labourMust agree to outpatient induction at 39 weeksNo relevant medical issues in or outside of pregnancyMust live within 30 min or 15 km of hospital and have transport to hospital at all times during induction periodHave a normal amniotic fluid index (AFI) at 39 weeks’ gestation (between 8 cm and 20 cm)Have a biophysical Profile Score (BPS) of 8/8Have a Bishop score < 6 at visit 2

#### Exclusion criteria

An individual who meets any of the following criteria will be excluded from participation in this study:Multiparous womenWomen with uterine scarWomen with low lying placentaWomen with BMI > 35 kg/m^2^Multiple gestationKnown fetal anomaly or fetal growth restriction or oligohydramniosKnown maternal health problem, e.g. hypertensive disease, cardiac disease, renal disease, diabetes, pulmonary disease, hepatic disease which would directly affect the risk status of the woman. This is assessed clinically on a case-by-case basis.Women with no transport to hospital or women who live > 30 min or > 15 km from the hospitalPatients who have difficulty understanding the required protocol and follow*-*up instructions (e.g. language barriers)Women < 39+0 or greater than 39+4 weeks’ gestation at the time of induction of labour (visit 2)◦ Gestational age will be based on initial dating scan between 7 and 14 weeks, which confirms gestational age by CRLAny factor which is a contraindication to induction of labourContraindications to trial treatment include patients that fall into any of the following categories:◦ If labour has started◦ If oxytocic drugs and/or other labour induction agents have *been* given◦ When strong prolonged uterine contractions would be inappropriate◦ Patients who have had previous major uterine surgery, e.g. caesarean section, myomectomy◦ Patients with a suspicion for cephalopelvic disproportionPatients with fetal malpresentation◦ Patients with suspicion or evidence of non-reassuring fetal testing◦ Who have had previous major surgery (e.g. other than biopsies and cervical abrasion) or rupture of the uterine cervix◦ When there is current pelvic inflammatory disease, unless adequate prior treatment has been instituted◦ Patients with hypersensitivity to dinoprostone or to any of the excipients listed in the Summary of Product Characteristics (SmPC) for Propess/Prostin◦ Patients with placenta previa or unexplained vaginal bleeding during the current pregnancy◦ Patients with evidence of infection, including genital tract infection

### Who will take informed consent? {26a}

It is the responsibility of the principal investigator at the recruitment site or another investigator delegated by the principal investigator to obtain written informed consent from each subject prior to participation in the trial, following adequate explanation of the aims, methods, anticipated benefits, and potential hazards of the study. Adequate time must be given for consideration by the patient before taking part.

The investigator or designee will explain that patients are under no obligation to enter the trial and that they can withdraw at any time during the trial, without having to give a reason for withdrawal. No clinical trial procedures will be conducted prior to taking consent from the participant. Consent will not denote enrolment into the trial.

A copy of the signed informed consent form will be given to the participant. The original signed form will be retained in the investigator site file (ISF) at the study site and a copy placed in the medical notes. The participant information materials and informed consent form are available from the corresponding author on request.

If new safety information results in significant changes in the risk/benefit assessment, the patient information leaflet will be reviewed and updated if necessary and subjects will be provided with the new patient information leaflet (PIL) in a timely manner and new consent obtained.

### Additional consent provisions for collection and use of participant data and biological specimens {26b}

N/A—no additional data or biological specimens are taken for the purposes of this trial.

### Interventions

#### Explanation for the choice of comparators {6b}

A vaginal dinoprostone delivery system (Propess) is a common method of cervical ripening for induction of labour. Dilapan-S is a synthetic osmotic hygroscopic gel which acts as a mechanical induction agent which has also been utilised in the setting of IOL. Whilst both have been the subject of a number of studies assessing efficacy and safety, no trial has compared the efficacy of both in relation to each other at 39 weeks in the outpatient setting.

#### Intervention description {11a}

Eligible patients will be prescreened from antenatal clinic lists and contacted to gauge interest in participating. An information leaflet will be sent to any interested parties. If the patient is interested having read the information, a clinic date will be assigned at approximately 38 weeks.

Visit 1: Clinic. The patient will attend a specialised home induction antenatal clinic appointment at approximately 38 weeks’ gestation. They will have vital signs measured and urinalysis carried out. A growth scan and fetal wellbeing scan will be performed by a sub investigator, and eligibility criteria will be assessed. Informed consent will be obtained from patients who meet inclusion criteria and do not meet exclusion criteria. They will then be randomised to one of 3 groups: Dilapan-S 12 h, Dilapan-S 24 h, or Propess 24 h. They will be allocated a date for IOL from 39+0 to 39+4 weeks’ gestation. Patients will be informed of their allocated group in advance of their allocated induction date.

Visit 1: Recruitment. Baseline assessments include:Obtain medical historyVital signsPhysical examination (if symptom driven)Abdominal examinationWeight, height, BMIUrinalysisUltrasoundRandomisation

Visit 2: Induction. Patients will be admitted to the hospital on the assigned induction date and will have vital signs and urinalysis performed. They will undergo a scan to assess biophysical profile. All eligibility criteria will be reassessed before commencement of IOL. Cardiotocograph (CTG) monitoring will be performed for at least 20 min prior to commencing IOL. The cervix will be examined, and Bishop score will be determined. Provided patients are still eligible; IOL will be carried out with the allocated device as per manufacturer’s instructions. CTG monitoring will be performed for 30 min (Dilapan-S) or 60 min (Propess) following application of the relevant intervention. Participants will then go home with a patient safety checklist and instructions for monitoring at home and instructions on when to return to hospital. Two phone calls will be made to the patients whilst at home to assess patient wellbeing.

Visit 2 assessments will include:Vital signsUrinalysisBishop scoreUltrasoundPhysical examination (if symptom driven)Abdominal examinationInvestigational medicinal product (IMP) administrationAdverse event reviewConcomitant medication reviewCTG

Visit 3: Reassessment. Patients will return to hospital at the allocated time, or before if clinically necessary (e.g. spontaneous rupture of membranes, vaginal bleeding, concerns re fetal movements or regular contractions). Vital signs will be measured, and urinalysis will be performed. A CTG will be performed. The IMP will be removed as per manufacturer’s guidelines, and reassessment of the cervix will be performed, and Bishop score will be determined. Clinical staff will assess whether the patient is suitable for artificial rupture of the membranes (ARM) or whether further ripening is needed. If further ripening is needed, Prostin gel at the dose of 1 mg will be given, a CTG will be performed, and the patient will be reassessed approximately 6 h thereafter. If deemed suitable for ARM, the patient will undergo same, a CTG will be performed, and the patient will be transferred to the labour ward when space is available. If required, oxytocin will be used to induce or augment labour as per hospital guidelines.

Visit 3 assessments will include:Vital signsBishop scorePhysical examination (if symptom driven)Abdominal examinationAdverse event reviewConcomitant medication reviewCTG

Visit 4: Delivery visit. Data is recorded from the electronic chart as per the schedule of events. Following delivery, a Maternal Satisfaction Questionnaire and stamped addressed envelope are sent to all participants to assess their experience throughout the trial.

Visit 4 assessments will include:Vital signsPhysical examination (if symptom driven)Delivery detailsMaternal Satisfaction QuestionnaireNeonatal outcomesAdverse event reviewConcomitant medication review

Visit 5: Six weeks following delivery, the participants are contacted, and data is recorded as per the schedule of events. This concludes the patient’s participation in the trial.

Visit 5 assessments will include:Maternal Satisfaction Questionnaire *(if unable to complete at visit 4)*Neonatal outcomes (if there has been a change since visit 4)Adverse event reviewConcomitant medication review

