## Discussion

When the proposal and protocol were in development throughout 2019 and 2020, the profound effect of COVID-19 on our healthcare system was not anticipated. The impact of the pandemic resulted in significant logistical difficulties for the HOME IND trial. Recruitment policies relied on telephone calls rather than in-person meetings. Restricted visiting hours were an inhibitory factor for people who may have otherwise consented to enrolment. Development of an active COVID-19 infection led to multiple participants being excluded at visit 2, resulting in a number of participants who had been randomised never receiving the IMP. Overall, we believe that the COVID-19 pandemic had a detrimental effect on both recruitment and the running of the trial, leading to an extended recruitment time in comparison to our pre-pandemic predictions.

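### Eligibility is finally settled at visit 2, after randomisation and with the arm known, which exposes the leading per-protocol analysis to selection bias of unknown size

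*Protocol article*

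**What the plan says.** All references are to the protocol article.

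- **Visit 1 (Intervention description {11a}).** "The patient will attend a specialised home induction antenatal clinic appointment at approximately 38 weeks’ gestation". Eligibility is assessed, consent is taken, and "They will then be randomised to one of 3 groups: Dilapan-S 12 h, Dilapan-S 24 h, or Propess 24 h".
- **Who learns the arm.** Pharmacy relays the allocation to the investigator (Implementation {16c}). For the woman: "Patients will be informed of their allocated group in advance of their allocated induction date". Investigators, medical staff and statisticians are not blinded ({17a}).
- **Visit 2 ({11a}).** "All eligibility criteria will be reassessed before commencement of IOL". Then: "Provided patients are still eligible; IOL will be carried out with the allocated device as per manufacturer’s instructions".
- **Criteria that belong to visit 2.** The inclusion list ties the Bishop score (below 6) to visit 2 and the amniotic fluid index (8 to 20 cm) to 39 weeks. The exclusion list applies the 39+0 to 39+4 window at visit 2 and names as a contraindication "If labour has started".
- **What has happened (Discussion).** Active COVID-19 infection led to several exclusions at visit 2, "resulting in a number of participants who had been randomised never receiving the IMP". No count or split by arm is given.
- **Analysis ({20a}).** The per-protocol population leads and intention-to-treat supports it. The margin is 10 percentage points, judged at one-sided 2.5% ({14}).

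**The concern.** Concealment protects the comparison only up to the point where the last decision on who counts is made. Here pharmacy allocation protects visit 1, but a second eligibility decision follows at visit 2 with the arm known. Part of it rests on an examiner's score of the cervix against a hard cut-off, and a woman who dislikes her allocation can withdraw in the interval. If either process differs by arm, the women who remain are no longer comparable, and the per-protocol set is made up of those women.

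The intention-to-treat set is not a complete safeguard. If it keeps everyone randomised, it avoids the selection but includes women who never received either device. Their outcomes cannot depend on the device, so they shrink any true difference. When Dilapan-S is truly worse, that shrinkage makes a claim of non-inferiority easier.

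**Working it through.** **1. The order of events**

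| Step | When | Arm known? |
|---|---|---|
| Eligibility check, consent, randomisation | Visit 1, about 38 weeks | No, until allocated |
| Arm relayed to investigator; woman told | Before the induction date | Yes |
| Bishop score, 39-week fluid index, labour not started, 39+0 to 39+4 window | Visit 2 | Yes |
| Device placed, if still eligible | Visit 2 | Yes |

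Most other criteria can be checked at visit 1 and are only rechecked later. Those in the third row cannot be settled before visit 2.

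**2. The plan's sample size, reproduced**

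Inputs from {14}: 70% with Propess; 75% and 80% with Dilapan-S, mean 77.5%; margin 0.10; one-sided 2.5%; power 90%; 2:1 once the Dilapan-S arms are combined. With the Farrington-Manning score variance, the restricted rates are 0.705 (Dilapan-S) and 0.805 (Propess):

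- s0 = √(0.805×0.195 + 0.705×0.295/2) = 0.511
- s1 = √(0.70×0.30 + 0.775×0.225/2) = 0.545
- n per group = (1.960×s0 + 1.282×s1)² / 0.175² = 94.3, so 95, and 3×95 = 285, as stated.
- 95×1.15 = 109.25, cut to 109, and 3×109 = 327, as stated.

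The arithmetic of the sample size is not at fault.

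**3. Loss of numbers**

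With equal loss in all arms from 327, power by the same method is 91.0% at 10% loss (294 left), 89.5% at 15% (278 left) and 87.7% at 20% (262 left). The 15% allowance roughly covers the numbers.

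**4. Selection in the per-protocol set (illustration only)**

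The article gives no loss rates, so these are assumptions: true success 70% in both groups, 20% lost from Dilapan-S and 10% from Propess, success p in those lost. Success among those retained = (0.70 − f×p)/(1 − f), where f is the fraction lost.

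| p | Dilapan-S retained | Propess retained | Spurious difference |
|---|---|---|---|
| 60% | 72.5% | 71.1% | +1.4 points |
| 50% | 75.0% | 72.2% | +2.8 points |
| 40% | 77.5% | 73.3% | +4.2 points |

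Swapping the loss rates reverses the sign. Equal losses (15% each, p = 50%) give no difference.

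**5. Dilution in the intention-to-treat set (illustration only)**

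Assume that all randomised women are kept (109 Propess, 218 Dilapan-S), that a fraction u in every arm is never induced with 70% success whatever the arm, and that the true difference in those treated is −10 points. Then:

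- apparent difference d = −0.10×(1 − u)
- SE = √(0.70×0.30/109 + p_T(1 − p_T)/218), with p_T = 0.70 + d
- chance of declaring non-inferiority = Φ((d + 0.10)/SE − 1.960)

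| u | d | SE | Chance |
|---|---|---|---|
| 0 | −10.0 points | 0.0550 | 2.5% |
| 10% | −9.0 | 0.0549 | 3.8% |
| 15% | −8.5 | 0.0549 | 4.6% |
| 20% | −8.0 | 0.0548 | 5.5% |

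With the plan's own assumed advantage for Dilapan-S, d = +0.075×(1 − u). At u = 0, 10% and 20% this is +7.5, +6.75 and +6.0 points, with SE 0.0522, 0.0524 and 0.0526. The same formula gives power of 91.8%, 89.2% and 86.1%. In that case dilution costs power and does not inflate the error.

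**The case against.** The case on the other side is substantial, and much of it limits the point.

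- **The two-stage check is planned.** The Bishop criterion is labelled as a visit-2 criterion and reassessment is scheduled, so this is not an oversight. That stands; the consequence for the leading analysis remains.
- **The COVID-19 exclusions are not evidence of arm-aware screening.** A reader might infer from the Discussion that the bias has been seen. It has not: the stated cause is infection, nothing ties it to arm, and exclusions unrelated to arm cost numbers without distorting the comparison. They show only that the pathway removes randomised women.
- **When the woman is told.** A reader might infer that she learns her arm at 38 weeks. The text says only that it is before the induction date. Nor does it say who scores the cervix; that the scorer may know the arm follows from the open-label design.
- **The 4.6% is not the trial's error rate.** It applies to the supportive analysis only, and the 15% in {14} is a non-adherence allowance, not a forecast of women never induced.
- **Both analysis sets are not shown to suffer selection.** Who enters the intention-to-treat set may be defined in the statistical analysis plan, which is not shown. If all randomised women are kept, that set has no selection problem of this kind.
- **Some protection exists.** Pharmacy allocates ({16b}, {16c}), withdrawals are recorded with reasons ({11b}), and the inflation largely preserves power.

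What remains is the order of events, which the text states plainly, and the fact that the analysis most exposed to it is the one that leads.

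**Conclusion.** The point holds as a design weakness that should be corrected where possible. Eligibility is finally decided after randomisation with the arm known, and the leading per-protocol analysis is exposed to selection. Confidence is high on the sequence and low on the bias itself: neither its direction nor its size can be derived from the document. The 1.4 to 4.2 points above show only what unequal losses could do against a 10-point margin.

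For the supportive analysis, with all randomised women kept, 10-20% never induced and equal outcomes among them in every arm, one-sided error at the margin is about 3.8-5.5% instead of 2.5%. If Dilapan-S is truly better, the effect is lost power. All these loss rates are assumptions.

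One contradiction needs no assumption: section {18b} says that deviation cannot occur, while {14} allows 15% non-adherence and the Discussion reports randomised women who were never treated.

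**What to change.** **Women still to be enrolled.** Take consent and book the date at visit 1, but have pharmacy randomise at visit 2, after eligibility is confirmed and before insertion. Women who labour or become ineligible in between are then never randomised. If randomisation must stay at visit 1, at least release the allocation only at that point in visit 2; this removes arm-aware screening, though women who become ineligible would still have been randomised.

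The cost is an amendment, with regulatory and ethics approval under {25}, and same-day arrangement of allocation and readmission time. The schedule gains no visit. Recruitment was due to end about 15 June 2023 and the article appeared on 23 February 2023, so the change reaches only the last women, and the report would have to state that two randomisation time points were used.

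**Women already randomised.** This part carries most of the weight and needs no new procedure:

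- Keep every randomised woman in the intention-to-treat analysis, using delivery data from the hospital chart.
- Report visit-2 exclusions and withdrawals before insertion by arm and reason.
- Read non-inferiority from the per-protocol and intention-to-treat results together, so that neither stands alone.
- Reconcile {18b} with {14} and the Discussion.

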#### Criteria for discontinuing or modifying allocated interventions {11b}

Participants will be withdrawn from the trial if:The patient requests to be withdrawn from the trialThe patient is deemed unsuitable for outpatient management.If it is deemed unsafe to allow the participant to return home once the IOL has commenced.Recording of any withdrawals will take place including the reason for withdrawal and the circumstances around the withdrawal.The trial will be stopped if there are any concerns for patient safety.

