##### Secondary outcome measures

Overall change in Bishop score before and after cervical ripeningRates of vaginal delivery at 36 h after insertion of either Propess or Dilapan-S®Rates of vaginal delivery at 48 h after insertion of either Propess or Dilapan-S®The need for second induction modalityRates of hyper-stimulation*Rate of failed inductionOverall length of stay in hospitalRates of adverse neonatal outcomeRates of adverse maternal outcomesMaternal satisfaction scores with the outpatient induction processCaesarean delivery rates, categorised by “overall rate”, “rate for failure to progress/failed induction”, and “rate for non-reassuring fetal testing”Analgesia use in each group, including rates of epiduralCompare rates of 39 weeks’ successful vaginal delivery in the outpatient setting to rates of successful vaginal delivery in the inpatient setting**.

*Defined as more than 7 contractions in a 15-min time period persistently for more than 30 min and requiring a medical intervention (such as a clinical decision to remove the Propess/Dilapan or administer a medication such as Terbutaline)

**Defined as a group of low-risk nulliparous women who did not undertake elective induction of labour at 39 weeks as part of this trial

The primary objectives will therefore assess the efficacy of achieving labour with each of the study induction methods. The secondary objectives will assess other efficacy measures, safety measures and maternal satisfaction scores which are important factors in deciding whether this is a feasible option long term, and risk stratification in this process. Although many studies have shown both induction mediums to be low risk, it is important to compare the outcomes as above in order to guide the best possible IOL methods and create the most appropriate protocol for women to undergo IOL.

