#### Implementation {16c}

A computer-generated randomisation sheet will be used to assign study participants to either Propess, Dilapan-S® 12 h, or Dilapan-S® 24 h groups at visit 1. The randomisation sheet will provide notification of the treatment package to be assigned to the participant and a log of each randomisation will be retained. The randomisation will be performed by the pharmacy department and relayed to the investigator. Subsequent to screening and consent procedures, the participants will be randomised to one of the three groups. The randomisation will use a block size of 4, and the random number seed-generator and generating program will be retained for reproducibility. The software SAS 6.4 will be used to generate the randomisation list.

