### Statistical methods

#### Statistical methods for primary and secondary outcomes {20a}

The analysis of the primary outcome will use a confidence interval (95% level of confidence) for simple differences in proportions. Non-inferiority will be determined on the lower confidence interval limit (equivalent to a one-sided 97.5% confidence interval). Conditional on non-inferiority being demonstrated, superiority will be determined. The analyses will be performed in the per-protocol population, supported by an intention-to-treat analysis.

Secondary outcomes will be compared using confidence intervals and hypothesis tests. However, these will be considered exploratory in nature. No adjustment for multiple testing will be performed.

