#### Adverse event reporting and harms {22}

All adverse events (AEs) occurring during the study observed by the investigator or reported by the subject will be recorded on the eCRF, except for those events that meet the definition of a non-reportable event. All AEs will be recorded from visit 2 until the 6 weeks postpartum follow-up visit.

The following information will be recorded: description, date of onset and end date, severity, assessment of relatedness to the study medication, other suspect medication or device, and action taken and outcome. Follow-up information should be provided as necessary. All AEs will be recorded with clinical symptoms and accompanied with a simple, brief description of the event, including dates as appropriate.

If the investigator suspects that the subjects’ disease has progressed faster due to the administration of the IMP, then they will record and report this as an unexpected adverse event. It will be left to the investigator’s clinical judgement whether or not an AE is of sufficient severity to require the subject’s removal from treatment. A subject may also voluntarily withdraw from treatment due to what she perceives as an intolerable AE. If either of these occurs, the subject must undergo an end-of-study assessment and be given appropriate care under medical supervision until symptoms cease or the condition becomes stable.

All serious adverse events (SAEs) will be reported to RCSI pharmacovigilance, except for those events that meet the definition of a non-reportable event. The principal investigator (PI) or appropriate designee is responsible for capturing all SAEs on appropriate trial specific forms and reporting to RCSI Pharmacovigilance within 24 h of first becoming aware of the event*.*

SAEs will be collected from visit 2 until the 6 weeks postpartum consultation and will be followed until resolution or until stabilised with sequelae.

Regarding AE/SAE in the baby, all NICU admissions will be captured as adverse events, with investigators assessing each admission to verify if it meets criteria for a SAE. All AEs that meet SAE criteria will also be recorded as such as per protocol.

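### Women judged unable to go home after insertion are withdrawn from the trial with no stated follow-up, which allows informative, arm-dependent loss of delivery and later outcomes

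*Protocol article*

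**What the plan says.** Section {11b} of the protocol article opens its list with "Participants will be withdrawn from the trial if". Apart from the woman's own request, it gives two grounds: being deemed unsuitable for outpatient management (no time limit stated), and "If it is deemed unsafe to allow the participant to return home once the IOL has commenced". For those who leave, it undertakes this: "Recording of any withdrawals will take place including the reason for withdrawal and the circumstances around the withdrawal".

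The timing comes from other sections:

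- Section {16c}, on implementation, fixes when the arm is assigned: "A computer-generated randomisation sheet will be used to assign study participants to either Propess, Dilapan-S® 12 h, or Dilapan-S® 24 h groups at visit 1".
- Intervention description {11a}: eligibility is rechecked and the device placed at Visit 2, after which "CTG monitoring will be performed for 30 min (Dilapan-S) or 60 min (Propess) following application of the relevant intervention", and only then does the woman go home.
- Blinding {17a}: the trial is open-label for investigators, medical staff and statisticians.

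On analysis, section {20a} states: "The analyses will be performed in the per-protocol population, supported by an intention-to-treat analysis". Section {20c} goes no further than exploring missing-not-at-random mechanisms. Section {18b}, on retention and complete follow-up, is marked not applicable on the ground that no deviation can occur.

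Section {22} records adverse events and serious adverse events from Visit 2 to six weeks postpartum. Where an adverse event leads to removal from treatment, it adds that "the subject must undergo an end-of-study assessment and be given appropriate care under medical supervision until symptoms cease or the condition becomes stable".

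**The concern.** The heading of {11b} is about stopping or modifying the allocated intervention, but its text removes the woman from the trial. The post-insertion ground is not an eligibility correction: eligibility has already been rechecked and the device is in place. It is a judgement made after randomisation and treatment, by staff who know the arm. The scheduled observation that could prompt it is twice as long for Propess as for Dilapan-S.

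Women withdrawn in this way may be at higher risk of caesarean delivery than those who go home. If they leave the primary comparison, and leave it unequally by arm, the estimated difference in vaginal delivery is no longer a comparison of randomised groups. The trial is also presented as an assessment of outpatient induction, and the article describes its secondary efficacy, safety and satisfaction measures as "important factors in deciding whether this is a feasible option long term". Being unable to go home after insertion bears directly on that question, yet it is not a listed outcome. An analysis plan cannot recover outcomes that the protocol does not direct staff to collect.

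**Working it through.** **1. The plan's own figure.** Inputs from Sample size {14}: Propess 70%; Dilapan-S 75% (24 h) and 80% (12 h), so (75 + 80)/2 = 77.5% combined; margin 10 points; one-sided 2.5%; power 90%; 1:1:1 allocation, hence 2:1 for combined Dilapan-S to Propess. The Farrington-Manning formula gives 94.3, so 95 per group and 3 × 95 = 285. Then 95 × 1.15 = 109.25, taken as 109 per group, and 3 × 109 = 327. Both stated figures reproduce (an unpooled variance would give 102 and 306). The point does not rest on a sample-size error.

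**2. What the article secures for a woman withdrawn after insertion.**

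| Item | Position |
|---|---|
| Reason for withdrawal | Recorded {11b}, so countable by arm |
| Adverse events before withdrawal | Inside the window; event review is part of Visit 2 {11a}, {22} |
| Adverse events after withdrawal | Window runs to six weeks {22}, but {11b} has ended her participation: unclear |
| Delivery and neonatal outcome | In the routine chart {11a}, {18a}; no instruction to collect after withdrawal |
| Six-week contact | No instruction after withdrawal |
| Per-protocol set (primary) | Would naturally omit her |
| Intention-to-treat (supportive) | Nothing removes her; nothing confirms her inclusion |

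**3. Shift in the estimated difference.** The article gives no withdrawal rate, so every input here is assumed: vaginal delivery 40% in withdrawn women and 75% in the rest, in both arms; withdrawn share wP = 3-10% (Propess) and wD = 0-2% (Dilapan-S).

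Among all treated women, the Dilapan-S minus Propess difference is [(1 − wD) × 0.75 + wD × 0.40] − [(1 − wP) × 0.75 + wP × 0.40] = 0.35 × (wP − wD). After removal both arms show 75%, so the difference becomes 0. The shift is 0.35 × (wP − wD), against Dilapan-S.

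- wP 5%, wD 1%: 0.35 × 4 = 1.4 points
- Smallest gap, 3% and 2%: 0.35 × 1 = 0.35 points
- Largest gap, 10% and 0%: 0.35 × 10 = 3.5 points

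**4. Chance of declaring non-inferiority.** With 109 Propess and 218 Dilapan-S women, let p be the true rate in all randomised women, w the withdrawn share and q their vaginal delivery rate (assumed 30-50%). The rate in those remaining is (p − wq)/(1 − w). The chance is Φ[(0.10 + pD − pP)/SE − 1.96], where pD and pP are the remaining-women rates and SE is the unpooled standard error on the remaining numbers.

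Worked case: truth at the margin, 2% Propess and 10% Dilapan-S withdrawn, q = 30%. Propess: (0.70 − 0.006)/0.98 = 0.708. Dilapan-S: (0.60 − 0.03)/0.90 = 0.633. The observed difference is −7.5 points instead of −10, and the chance is 6.6%.

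| Withdrawn, Propess / Dilapan-S | Truth 70% vs 60% (at the margin) | Truth 70% vs 77.5% (design) |
|---|---|---|
| 0 / 0 | 2.5% | 91.8% |
| 5% / 5% | 2.0% | 92.3-93.0% |
| 10% / 2% | 0.4-1.0% | 76.6-84.3% |
| 2% / 10% | 3.3-6.6% | 97.0-98.9% |

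Heavier withdrawal from Propess costs power. Heavier withdrawal from Dilapan-S inflates false non-inferiority. Equal withdrawal changes little.

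**The case against.** The other side has a good deal in its favour. Four stronger readings are tempting, and the document does not support them.

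- *Early treatment harms vanish.* They need not. Event review is part of Visit 2, reporting runs from then, and serious events are followed to resolution or stabilisation. What is unclear is follow-up after withdrawal. Hyperstimulation is also defined as persisting for more than 30 min and needing intervention, so it cannot be fully met within the Dilapan-S monitoring period and only partly fits the Propess one. Events while the device is in place for 12 or 24 h are largely outside this rule.
- *The share of women who can go home cannot be estimated.* It can, because {11b} records the reason for each withdrawal.
- *The intention-to-treat analysis is broken.* No section removes withdrawn women from it. {14} attaches the 15% non-adherence allowance to the intention-to-treat number, which suggests that women who depart from protocol are kept. Detailed population definitions may be in the analysis plan, which is not at hand.
- *Being kept in hospital is a primary-outcome failure.* Under Primary outcome measure, the endpoint is failure of vaginal delivery at any time, so she may still succeed.

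In addition, ruptured membranes, bleeding or regular contractions at home lead to an early Visit 3 within the trial, so the affected group may be small.

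What this leaves standing is that {11b} says withdrawn from the trial, no section restores these women to outcome collection, and the primary analysis set is the one most likely to drop them.

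**Conclusion.** The concern holds as a should-fix. Section {11b} does not separate leaving outpatient management from leaving the trial. Followed as written, it permits informative and arm-dependent loss of delivery, neonatal and later outcomes in treated women, with most effect on the per-protocol primary analysis. It does not establish that such loss will occur.

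Size and direction are unknown. The 0.35-3.5 point shift (1.4 at 5% against 1%) rests wholly on assumed withdrawal and delivery rates, and in that scenario it works against declaring Dilapan-S non-inferior. False non-inferiority rises only under the opposite imbalance, to 3.3-6.6% in the case tabulated. A reader might infer that the rule necessarily favours Dilapan-S or invalidates the trial; neither follows.

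**What to change.** The change concerns data and analysis only; the clinical decision to keep a woman in hospital is not questioned.

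1. Reword {11b}: *a woman who leaves outpatient management after insertion remains in the trial unless she withdraws consent.*
2. State that delivery, neonatal, adverse-event and six-week data are still collected for her, from the chart and the planned Visit 5 contact.
3. State that she is analysed in her randomised arm in the intention-to-treat analysis, and say how the per-protocol set treats her.
4. Tabulate, by arm, women who did not go home after insertion.
5. Reconcile {11b} with {18b} (no deviation possible), {20a} (analysis sets) and {22} (event window and end-of-study assessment).

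The cost is a protocol wording change and one extra table. The delivery data already sit in the hospital chart, and no further visits or participants are needed. The one small drawback is that reported success rates may be slightly lower.
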